### Interventions

#### MemFlex

We have previously piloted the MemFlex programme with individuals in remission from depression.^34^ The intervention will be delivered as per the pilot trial and the trial evaluating the intervention in those with current depression.^35^ The programme aims to improve the flexibility of autobiographical retrieval processes, to improve the ease with which individuals can access and move between specific and general personal memories, and to train away a bias towards negative memories. This is achieved through repeated completion of cued recall tasks which use positive and neutral cues. The training exercises are introduced in an initial face-to-face session with a researcher, and the participant is then required to complete two times weekly sessions of training over a 4-week period. During the initial session, the researcher provides information about the role of autobiographical memory in depression, including the different types of autobiographical memories (eg, specific event memories, and the generalised themes that link together a series of events) and their presumed role and importance in daily life. The rationale for MemFlex is then introduced. The researcher then assists the individual to complete practice exercises, and provides feedback and encouragement to ensure that the individual understands the tasks. The session lasts between 45 and 60 min. The participant will also receive a telephone call from the researcher halfway through the time set to complete the workbook to answer any questions, and address any difficulties the individual may be having with the workbook. The participant is also encouraged to contact the researcher with any questions about the workbook content.

The MemFlex workbook is separated into eight sessions. The early sessions of the workbook focus on reducing the bias towards negative and general memories experienced in depression by promoting the retrieval of both specific and general memories of neutral and positive valence. This involves repeated cued-recall exercises using neutral and positive cues. Next, the workbook encourages the individual to elaborate the specific emotional details attached to positive memories, again using repeated retrieval tasks. This seeks to improve the reduced vividness of positive memories experienced in depression.^18^ The final workbook sessions involve completion of exercises that require the participant to explicitly link specific event memories with a general theme, and in reverse, to identify individual event memories that form a general theme. To do this, individuals must explicitly switch between retrieving specific and general memories to the same cue, thereby promoting flexibility in movement between the different memory types. When completed with positive cues, this type of exercise also aims to promote positive generalisations about the self. Exercises are repeated throughout the workbook to give participants practice in using the different skills. There are additional exercises at the end of the workbook that the participant can choose to do after the study has ended. While participants are encouraged to continue to apply their new skills in their everyday life, completion of the additional workbook exercises is optional.

#### Psychoeducation

Participants in the psychoeducation condition will also attend a 45–60 min face-to-face session, followed by the completion of a workbook over a 4-week period. The initial session will provide information on the causes of depressive relapse, and the individual’s experience of relapse will be discussed between the researcher and participant. The eight-session workbook will then be introduced.

The psychoeducation workbook is a relapse-focused adaptation of that used in a previous trial for those with MDD.^35^ The workbook presents theory on different cognitive and lifestyle factors that are associated with depression which may persist between depressive episodes, and promote the experience of low mood in the future. These include poor sleeping patterns, worry and perfectionism. After the relevant theory is explained, each component of the workbook will offer tips for improving each factor, and an exercise which encourages the participant to reflect on whether these factors occur in their life. Four multiple-choice questions are also asked at the end of each session to ensure participant engagement, and to match the completion of workbook exercises against the MemFlex condition. Interventions are matched for time burden.

#### Treatment integrity

Both workbooks are available from the corresponding authors on request, and will be made available online if their efficacy is demonstrated. Researchers will be trained and supervised by a clinical psychologist (CH) to administer the manualised initial sessions. Sessions will be audio-recorded, and 15% of these will rated for adherence to the manual by a researcher independent from the project. At the end of the initial session, participants will complete the Credibility Expectancy Questionnaire—Patient Version^39^ to index any difference in treatment expectations between the two intervention conditions. Progress on the workbook will be checked halfway through the 4 weeks provided for workbook completion. If the individual is behind on workbook completion, any difficulties in completing the workbook will be briefly addressed, and trial management records will be updated with an anticipated finish date. A member of the research team will call the individual the week before the anticipated finish date to set an appointment time for the postintervention assessment. To ensure adherence, the workbook will also be viewed at postintervention to ensure all materials have been attempted. The number of completed sessions will be recorded.

### Measures

#### Cognitive target

We anticipate that the MemFlex programme will improve, and maintain improvement in, memory flexibility relative to psychoeducation. We will therefore administer the Autobiographical Memory Test with Alternating Instructions (AMT-AI^8^) at all assessments. The AMT-AI requires individuals to recall either specific or general memories in response to neutral, positive and negative cue words. Participants are asked to retrieve specific memories to a block of six cue words, general memories for a block of six cues and finally a block of 12 cues in which the individual must alternate between retrieval of specific and general memories. The cues are randomised to blocks, and the order in which the blocks are presented is also randomised. The main outcomes are the number and proportion of correct responses for each block (ie, specific, general, alternating).

#### Primary clinical outcomes

The primary clinical outcomes are number of depression-free days from postintervention to 12-month follow-up, and number of days until depressive relapse, both according to the LIFE.

#### Secondary clinical outcomes

The secondary clinical outcomes are depressive status at 12-month follow-up, again measured using the LIFE and symptoms of depression at 12-month follow-up as indexed on the Beck Depression Inventory II (BDI-II^40^).

#### Additional process measures

We have previous evidence to suggest that MemFlex will impact rumination, social problem solving and cognitive avoidance in samples remitted from depression.^34^ We will therefore assess whether these factors may mediate the impact of MemFlex on our primary and secondary outcomes. Rumination will be measured using the Rumination Response Scale,^41^ cognitive avoidance will be measured using the Cognitive Avoidance Questionnaire^42^ and social problem solving will be indexed on the short version of the Means-Ends Problem-Solving (MEPS) task.^43^ We will also assess verbal fluency using the Verbal Fluency Task^44^ to determine whether the programme impacts the fluent retrieval of verbal information. Each of these measures possesses adequate psychometric properties and has been previously used in evaluation of autobiographical memory interventions.^7 34 35^ Parallel forms of these measures will be counterbalanced and administered at all time points.

### Methodological aspects

#### Power analysis

As this is an exploratory, early-stage randomised controlled platform trial (in accordance with recommendations for the evaluation of complex interventions; Medical Research Council (MRC), 2000), we aim to generate estimates of the range of likely effect sizes of MemFlex (relative to psychoeducation) on our primary clinical outcomes. This can then be used to inform a power calculation for a fully powered later-phase trial. Our prior experience with autobiographical memory-based interventions for depression (eg, refs 29 34 35 45) suggests that 25 participants per condition will provide a plausible range of point estimates. Given the long-term follow-up we implement, we aim to recruit 35 participants in each condition (70 participants in total) to allow for up to 25% attrition.

#### Data collection and blinding

Participants will be assessed at baseline, and then again at postintervention, and at 6-month and 12-month follow-ups after the intervention has been completed. All sessions will be completed at the MRC Cognition and Brain Sciences Unit in Cambridge, UK, except in the case that a participant moves away from Cambridge before the completion of all assessments. In these cases, 6-month and 12-month follow-up assessments may be completed over the telephone. As the AMT-AI is unable to be completed over the telephone, it will not be administered at follow-up for these participants. Research staff completing the assessments will be supervised by a clinical psychologist (CH) and inter-rater reliability will be completed for the AMT-AI and MEPS to ensure data quality and protection from bias. Bias will also be protected against at all assessments through use of research staff whom are blind to experimental condition.

#### Statistical analysis plan

The trial statistician is blind to study objectives, and will complete all analyses in accordance with CONSORT standards. No interim analyses are planned during data collection. Between-group difference on our primary clinical outcome of number of depression-free days will be analysed using an independent samples t-test, or analysis of covariance if necessary to account for any baseline differences. Time to depressive relapse will be compared between groups using Cox regression survival analysis. Analysis of our cognitive target variable, secondary clinical outcomes and additional process measures will be analysed using analysis of variance (ANOVA) with time (pre, post, 6 and 12 follow-up) as a within-subjects factor, and condition (MemFlex, psychoeducation) as a between subjects factor. Any baseline differences in the cognitive target, symptom severity on the BDI-II, concurrent treatment or demographics will be covaried in analyses. Diagnostic status at 12-month follow-up will analysed using logistic regression. Residual depression symptoms and number of previous episodes (as an index of depression severity), and score on the AMT-AI (as an index of bias severity) at preintervention will be explored as moderators of treatment efficacy by computing product variables that will be analysed using linear regression. Finally, we will explore mechanisms of change by determining whether intervention effects are mediated by change on the AMT-AI and the other process measures. Indirect effects will be analysed using bootstrapped samples in the Process statistical package. Intent-to-treat analysis will be used for those lost to attrition by using multiple imputation to account for missing data. The number of imputed datasets will approximate the percentage of missing data.^46^ Any exploratory, per-protocol analyses will use data from participants who have completed six out of the eight workbook sessions. Exploratory ANOVAs will also be completed to explore between-group difference in pre-to-post intervention change on the separate AMT-AI blocks, to determine whether MemFlex may have a larger impact on specific, categoric or alternating recall.

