### Participant allocation

Random allocation to condition using computer-generated, quasi-random numbers will completed by the trial statistician (PW), who is blind to study objectives. Once a participant has provided informed consent and completed the preintervention assessment, the researcher completing the initial session will open a sealed, opaque envelope to reveal condition allocation. This process is demonstrated in the Consolidated Standards of Reporting Trials (CONSORT) diagram (see figure 1).

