### Trial management

The trial management committee will be formed by TD, CH and trial statistician (PW). The trial coordinator (CH) will complete data checks to ensure data quality.

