### Confidentiality and access to data

Only the trial coordinator and trial statistician will have access to the final dataset. Data will be securely stored in de-identified form on-site, and in encrypted electronic format. Personally identifiable information will be stored separately to the trial data, and will only be accessible via a dedicated access server. Once the data have been analysed and the trial is published, the final dataset will be deposited in de-identified form into the research unit’s online data repository, along with the used statistical code.

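### The statistician's stated blindness to the objectives is hard to square with the listed roles and says nothing about allocation, while the depression-free-days model is left to depend on observed baseline differences

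*Protocol article*

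**What the plan says.** All of this is in the Protocol article.

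- **Blindness claim.** The Statistical analysis plan section opens with "The trial statistician is blind to study objectives", and the same sentence gives this person every analysis. The Participant allocation section makes the same claim about blindness.
- **Allocation.** "Random allocation to condition using computer-generated, quasi-random numbers will completed by the trial statistician". It is revealed later, when "the researcher completing the initial session will open a sealed, opaque envelope to reveal condition allocation".
- **Committee.** The Trial management section reads "The trial management committee will be formed by" three people, one of whom is the trial statistician.
- **Data access.** "Only the trial coordinator and trial statistician will have access to the final dataset".
- **Primary model.** The number of depression-free days "will be analysed using an independent samples t-test, or analysis of covariance if necessary to account for any baseline differences". A later sentence in the same section says that baseline differences in memory flexibility, BDI-II severity, concurrent treatment or demographics will be covaried. Neither sentence says how large a difference must be, or how it is judged.
- **Other analyses for the same person.** Product-term moderators, bootstrapped mediation through the AMT-AI and process measures, and a comparison of MemFlex's effect across the AMT-AI blocks.
- **Blinding to condition.** The section Data collection and blinding claims it for the assessing staff. The article does not claim it for the analyst.

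**The concern.** The article offers the statistician's unawareness of the aims as a protection, and it introduces the analysis plan. Two things weaken it. First, someone who helps manage the trial and must specify which variables might moderate or mediate the benefit of MemFlex will know what the trial is trying to show. Second, the protection that bears on analyst bias is not knowing which participant is in which arm, and the statement does not reach that.

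This would be a wording matter only if the primary model were fixed. It is not: the switch from t-test to covariance analysis and the covariates to include both follow from looking at the arms side by side. A person not stated to be blind to arm therefore has room for judgement on a primary outcome. At stake is the effect estimate that the trial exists to supply for planning a later study, and any p-value or interval attached to it.

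**Working it through.** **1. The roles side by side**

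| Role | Does it conflict with blindness to objectives? | Does it bear on knowledge of arm? |
|---|---|---|
| Generates the allocation list | No; a list can be made without knowing the hypothesis | Yes; this person made the list |
| One of three committee members | Hard to reconcile | Not stated |
| Runs moderator, mediation and MemFlex-framed analyses | Hard to reconcile; these analyses spell out the hypotheses | Not stated; arms could be coded |
| Access to final dataset | No | Not stated; arms could be coded |

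The tension comes from rows two and three.

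**2. Arm sizes**

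The plan wants 25 per arm and allows 25% attrition: 25/(1 − 0.25) = 33.3, so 34. The plan states 35, and 35 × 0.75 = 26.25 remain. The stated figure is consistent. The checks below use 35 and 25 per arm.

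**3. How often the switch would be triggered**

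If a baseline difference means p<0.05, the chance of at least one among k independent covariates under proper randomisation is 1 − 0.95^k. For k = 4 this is 18.5%, and for k = 5 it is 22.6%. The plan gives neither k nor the cut-off; both are assumptions.

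**4. False-positive rate under no effect**

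Assumptions, none from the documents: two-sided 0.05; normal outcome; four independent covariates with weights 0.1, 0.2, 0.3 and 0.4; 3,000 to 10,000 simulated trials per setting. With 10,000 trials the simulation standard error is about 0.3 points near 10% and 0.2 points near 4.5%. Ranges cover runs at both arm sizes and with different residual scaling.

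| How the model is chosen | Rejection rate |
|---|---|
| t-test always | 4.5% to 5.5% |
| ANCOVA always, all four covariates | 4.8% to 5.2% |
| ANCOVA only for covariates with baseline p<0.05 | 4.3% to 4.5% |
| Smallest p of six models (t-test, four single-covariate ANCOVAs, one with all four) | 9.2% to 10.7% |
| Any of the six significant in favour of MemFlex | about 5%, against a nominal 2.5% |

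A narrower choice, between the t-test and one ANCOVA at 25 per arm, gives 5.5%, 6.3%, 7.3% and 8.0% when the covariate correlates 0, 0.3, 0.5 and 0.7 with the outcome. With five candidate covariates of which one is prognostic, the mechanical p<0.05 rule gives 5.0%, 4.6%, 4.2% and 3.9% at the same correlations.

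**5. Effect on the estimate**

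Always taking the model most favourable to MemFlex moves the mean null estimate from 0 to about 0.08 SD at 35 per arm and 0.10 SD at 25 per arm. The t-test standard errors are √(2/35) = 0.239 and √(2/25) = 0.283 SD, so the shift is about a third of a standard error (0.08/0.239 = 0.33; 0.10/0.283 = 0.35).

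**6. What a fixed adjusted model gains**

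The four weights explain 0.01 + 0.04 + 0.09 + 0.16 = 0.30 of the variance. At 35 per arm the standard error falls from 0.239 to about √0.70 × 0.239 = 0.200 SD, before the small cost of estimating four coefficients.

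**The case against.** The strongest reply has four parts.

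- **The claim is not flatly contradicted.** Making a random list needs no knowledge of the hypothesis, and committee membership does not say what was disclosed to the statistician. This stands for the list. For the committee and the named analyses, the statement remains implausible rather than disproved.
- **Coded arms may be in the full protocol.** The article neither states nor excludes them, and an article commonly leaves such detail out. This stands. A reader might infer that the analyst will be unblinded, or that no safeguard exists; the text supports neither. It supports only that the one analyst safeguard it names does not address allocation.
- **The plan does not permit picking by result.** It ties the switch to baseline differences and names the domains. This also stands. A reader might take 10% as the plan's error rate, but that figure ignores baseline imbalance altogether and counts rejections in both directions. Followed mechanically at p<0.05, the rule is slightly conservative. What remains is that no cut-off is given, so the rule cannot be followed mechanically as written.
- **The trial is exploratory and states no alpha.** True, and it lowers the weight of the error rates. It does not remove the point, because the product is an effect estimate and selection moves that estimate too.

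Concealment by sealed envelope, assessors blind to condition and the absence of interim analyses are untouched. The t-test/ANCOVA switch is written for one of the two primary outcomes. Time to relapse is fixed as Cox regression, though the general sentence on covarying baseline differences may reach it.

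**Conclusion.** The point holds in a limited form. The blindness statement is hard to reconcile with the statistician's committee seat and assigned analyses, and it offers nothing on knowledge of allocation. The practical weakness is that the depression-free-days model and its covariates depend on observed baseline differences without a threshold.

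Under the assumed weights, model set and two-sided 5% level, the false-positive rate runs from about 4% (mechanical imbalance rule) to about 10% (free choice of six models). Neither is the nominal 5%, which a model fixed in advance keeps whoever runs it. The worst-case shift in the estimate is 0.08 to 0.10 SD. Other covariate counts or weights would change these figures. Nothing in the article suggests that selective choice was intended. This is a free or cheap improvement.

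**What to change.** 1. **Fix the model.** Replace the t-test-or-ANCOVA wording and the baseline-difference rule with one ANCOVA for depression-free days. Name its covariates in advance from variables already collected, for example baseline BDI-II, baseline AMT-AI and number of previous episodes. Say whether the same covariates enter the Cox model. The rule has to be replaced, not just applied blind, because differences between arms cannot be judged on data pooled over arms.
2. **Correct the claim.** Remove or reword the statement on blindness to objectives in both the Participant allocation and the Statistical analysis plan sections, and say whether the analyst is blind to allocation.
3. **Recode the file.** Give the analyst arms labelled A and B with new participant numbers. The new numbers are needed because the analyst made the original list. Someone else holds the key until the model is locked.

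Cost: a few sentences and one recoded file. No extra participants, visits or measures are needed. Under the assumed weights the fixed model also narrows the standard error from about 0.24 to about 0.20 SD at 35 per arm.

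### The secondary BDI-II outcome is set at 12 months, but the planned ANOVA counts the pre-treatment score as an outcome level and neither of its standard terms is the 12-month difference

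*Protocol article*

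**What the plan says.** All references are to the protocol article.

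- **Outcome definition (Secondary clinical outcomes).** "The secondary clinical outcomes are depressive status at 12-month follow-up, again measured using the LIFE and symptoms of depression at 12-month follow-up" on the BDI-II. Both secondary outcomes are tied to one visit.
- **Model (Statistical analysis plan).** "Analysis of our cognitive target variable, secondary clinical outcomes and additional process measures" go to one model, and are to be "analysed using analysis of variance (ANOVA) with time (pre, post, 6 and 12 follow-up) as a within-subjects factor, and condition (MemFlex, psychoeducation") as the between-subjects factor. The section does not say whether the condition main effect or the condition-by-time interaction is to be read, and names no 12-month contrast.
- **Covariate rule (same section).** "Any baseline differences in the cognitive target, symptom severity on the BDI-II, concurrent treatment or demographics will be covaried in analyses".
- **Binary secondary outcome (same section).** "Diagnostic status at 12-month follow-up will analysed using logistic regression".
- **Cognitive target (Cognitive target).** "We will therefore administer the Autobiographical Memory Test with Alternating Instructions (AMT-AI^8^) at all assessments". No single visit is singled out for it, nor for the process measures.

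**The concern.** The stated outcome and the stated model do not match. A reader of the BDI-II result wants the between-arm difference one year on. A two-by-four ANOVA offers two standard condition terms, and neither is that difference.

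The pre-treatment score also has an unsettled role. It is always an outcome level, although treatment cannot have affected it. For the BDI-II and the AMT-AI it may become a covariate as well, depending on whether a baseline imbalance is seen. The adjustment is therefore not fixed in advance, and at the pre level the score would be regressed on itself.

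At stake is the interpretability of the BDI-II effect estimate and, for the AMT-AI and process measures, a cleaner use of baseline.

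**Working it through.** **The plan's own figure.** The Power analysis section wants 25 per arm with data and allows for up to 25% attrition: 25/(1 − 0.25) = 33.3, so 34. The stated 35 per arm covers this (35 × 0.75 = 26.25). The sample size is reproduced and plays no further part, except that 25 and 35 per arm bracket the numbers analysed.

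**Assumptions (the document gives none of these).** Standard deviation 1 at every visit; equal correlation ρ between visits of 0.3 to 0.7; two-sided 5% tests; a largest effect of 0.50 SD; n = 25 per arm unless stated. Write d_post, d_6 and d_12 for the arm differences after treatment. Randomisation makes the expected difference at pre zero.

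**What the main effect estimates.** (0 + d_post + d_6 + d_12)/4.

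| Pattern (post, 6, 12 months) | Main effect | Relative to d_12 |
|---|---|---|
| Constant: 0.50, 0.50, 0.50 | 1.50/4 = 0.375 | 75% |
| Growing: 0.125, 0.25, 0.50 | 0.875/4 = 0.219 | 44% |
| 12 months only: 0, 0, 0.50 | 0.50/4 = 0.125 | 25% |
| Fading: 0.50, 0.25, 0.125 | 0.875/4 = 0.219 | 175% |

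The factor 3/4 is fixed only relative to the average of the three post-treatment visits. Relative to 12 months, the error can go either way.

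**What the interaction tests.** Its noncentrality is (n/2) × Σ(d_j − d̄)²/(1 − ρ), on 3 and 144 degrees of freedom. For the constant pattern at ρ = 0.5: 12.5 × 0.1875/0.5 = 4.69. It asks whether the arm difference changes anywhere across four visits, and returns no 12-month estimate.

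**What a 12-month ANCOVA estimates.** d_12 itself, with SE = √(2(1 − ρ²)/n). At ρ = 0.5 this is √(2 × 0.75/25) = 0.245.

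**Power, n = 25 per arm, d_12 = 0.50.**

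| ρ | 12-month ANCOVA | Interaction, constant | Interaction, growing | Main effect (no covariate), constant |
|---|---|---|---|---|
| 0.3 | 44% | 30% | 22% | 47% |
| 0.5 | 52% | 41% | 30% | 38% |
| 0.7 | 68% | 63% | 48% | 31% |

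With 35 per arm, d_12 = 0.6 and ρ = 0.5, the ANCOVA has about 82% power. The interaction has about 73% for a constant effect and 58% for 0.2, 0.4, 0.6. At ρ = 0.7 and a constant effect, ANCOVA and interaction both reach about 93%.

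**Baseline as covariate and outcome level together.** Regressing the pre score on itself and on condition leaves a condition coefficient of exactly zero at that level. In the constant pattern at ρ = 0.5 the main effect stays at 0.375, while its SE falls from √(2 × (1 + 3 × 0.5)/(4 × 25)) = 0.224 to 0.137. The latter is 3/4 of 0.183, the SE of an ANCOVA on the average of the three post-treatment visits. Power is then 77%, the same as for that ANCOVA, but the effect size is still a quarter too small.

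**The case against.** The strongest reply is that the plan never says the main effect will be read. The Cognitive target section expects a gain that is then held, and the exploratory analyses compare the arms on change from pre to post. Both suggest the interaction, and an interaction contrast is not diluted. This stands. A reader might infer that the BDI-II estimate is bound to be diluted, but the text does not support that. Dilution needs the main effect to be the term read, and if benefit fades the main effect overstates the 12-month difference. The article itself lists the lack of booster sessions as a possible limit on long-term efficacy. What remains is that neither term is the defined outcome.

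Second, power does not always favour the 12-month contrast. With baseline covaried and a constant effect, the main effect has more power (77% against 52% above; about 97% against 82% at 35 per arm and 0.6 SD). Even without the covariate it is slightly ahead at ρ = 0.3. Under fading the interaction is the more powerful. This also stands, but these tests address other quantities.

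Third, the double use of baseline need not bias. With baseline slopes allowed to differ by visit, the condition contrast of 12 months minus pre equals the 12-month ANCOVA estimate. True, but the plan names no such contrast, and it adjusts only if an imbalance is seen.

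Fourth, contrasts and intervals are often left to a fuller analysis plan. That would answer a complaint about missing detail. Here the article states a model, and the model does not fit its own outcome definition.

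A reader might also infer that depressive status is assigned to both ANOVA and logistic regression, because it is a secondary outcome. The specific logistic regression sentence governs, so there is no error.

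**Conclusion.** The point holds in a limited form. For the BDI-II, the stated analysis does not estimate the stated 12-month outcome. The main effect is 75% of a constant post-treatment effect, and may fall well below or above the 12-month effect if the effect grows or fades (44% and 175% in the examples). The interaction is an omnibus test. Under the assumed correlations of 0.3 to 0.7 and 25 to 35 per arm, the 12-month ANCOVA has equal or higher power than that interaction when the effect is constant or growing. The advantage runs from practically nothing to more than 20 percentage points.

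For the AMT-AI and the process measures no 12-month mismatch is claimed, since they are not defined at that visit. What applies to them is the use of the pre score as an outcome level and, for the AMT-AI, its conditional second role as covariate.

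A reader might infer that the trial's main purpose, estimating effect sizes, is compromised. It is not: the Power analysis section ties that aim to the primary clinical outcomes, which are analysed by t-test or ANCOVA and by Cox regression. The sample size is also untouched. Importance is low to moderate.

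**What to change.** 1. **BDI-II:** name the between-arm difference at 12 months, with a 95% confidence interval, as the reported estimate. Obtain it from ANCOVA on the 12-month score, or from a repeated-measures or mixed model of the post, 6-month and 12-month scores with condition by time.
2. **Baseline:** always include the baseline score of the measure as a covariate, whether or not the arms differ, and never as an outcome level.
3. **AMT-AI and process measures:** use the same baseline-adjusted model of post-randomisation scores, and report the difference at each visit.
4. **Wording:** optionally exclude diagnostic status from the ANOVA sentence, so that the logistic regression is plainly its only analysis.

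The cost is a few sentences and standard software. No new data or participants are needed, the planned multiple imputation can be kept, and ANCOVA is already foreseen for depression-free days. The one trade-off is that, if the effect is constant, a 12-month contrast has less power than an average over the post-treatment visits. That average can be reported alongside from the same model.
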